## Outcomes

Primary outcome measures: 1a) a between-group difference in gut microbial alpha diversity will be measured using Shannon diversity index at the 7th day and 1b) a between-group difference in the concentration of fecal metabolites (short chain fatty acids) will be quantitatively measured using non-targeted liquid chromatography-mass spectrometry (LC–MS) at the 7th day.

Secondary outcome measures: 2a) between-group differences in other diversity indicators of gut microbiota, including Simpson index (an indicator of species richness and evenness less affected by rare species than Shannon index) and Chao1 index (estimated total number of species) at the 7th day; 2b) between-group differences in alpha diversity of gut microbiota measured using Shannon index, Simpson index and Chao1 index on the 14th, 21st and 28th days of life; 2c) Between-group differences in the concentration of fecal metabolites quantitatively measured by non-targeted LC–MS at the 14th, 21st and 28th days of life; 2d) proportion of gut microbiota at phylum and genus level; 2e) gut microbial beta diversity explaining between-sample dissimilarity calculated using the Vegan package; and 2f) correlation between the comparative dominant flora and metabolites (Table 1).

**Table 1 Tab1:** Outcomes, measures and methods of analysis

Outcome	Hypothesis	Outcome Measure	Methods of Analysis
**1.Primary** 1a A between-group difference in Shannon diversity index at the 7th day	OAC increases Shannon diversity and metabolites of gut microbiota	Shannon index (continuous)	Individuals: Wilcoxon text; Intergroup: T/Wilcoxon text
1b A between-group difference in fecal metabolites at the 7th day		Short chain fatty acids (continuous)	Individuals: FC, PCA/PLS-DA Intergroup: T/Wilcoxon text
2.** Secondary** 2a Between-group differences in other alpha diversity indexes (Simpson, Chao1) at the 7th day	OAC increases other alpha diversity and beta diversity, and changed the proportion of gut microbiota from birth to day 28. There is a Correlation between dominant microbiota and metabolites	Simpson index, Chao1 index (continuous)	Individuals: Wilcoxon text; Intergroup: T/Wilcoxon text
2b Between-group differences in Shannon index, Simpson index and Chao1 index at the 14th, 21st and 28th days of life		Shannon index, Simpson index, Chao1 index (continuous)	Individuals: Wilcoxon text; Intergroup: T/Wilcoxon text

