### Statistical analysis

Intention to treat (ITT) method will be used for statistical analysis. Baseline maternal and infant demographic and clinical characteristics of OAC group and placebo group will be compared using chi-square or Fisher’s exact test (such as infant sex, mode of delivery and presence or absence of chorioamnionitis) and t-test or Wilcoxon test for continuous variables. After removing low-quality sequences, original data will be analyzed following the steps of 16S rRNA discovery, clustering and identification. The number of operational taxonomic units (OTUs) will be calculated for each sample at a 97% sequence similarity level. A specific taxonomic unit will represent a specific species. Subsequently, a sparse curve will be drawn based on the results of OTUs generated using sample sequencing. Wilcoxon test will be used to analyze the diversity and richness of microbiota within individuals. A t-test or Wilcoxon test will be used to compare alpha diversity (Shannon index, Simpson index, and Chao1 index) between the two groups of infants with and without OAC intervention within four weeks of birth. Repeated measures analysis of variance (ANOVA) (for normally distributed data) or Kruskal Wallis test (for non-normal data) will be used to evaluate the microbial alpha diversity at different time points. The proportion difference of gut microbiota at the phylum and genus levels will be calculated using chi-square or Fisher's exact test. Values with *p* < 0.05 will be considered statistically significant. Beta diversity will be calculated using the Vegan package, and a principal co-ordinates analysis (PCOA) based on Bray–Curtis distances will be plotted. Adonis permutational multivariate analysis of variance of Bray–Curtis distances with 9999 permutations will be used to compare microbial community structure between each of the two groups.

Redundancy analysis (RDA) will be performed using the Vegan package to define the factors that could significantly affect gut microbial composition in each group. We will use Linear discriminant analysis (LDA) of effect size (LEfSe) to determine the most discriminant taxa between the two groups. If the effect of OAC intervention on gut microbiota is less than that of other confounding factors (delivery mode, antibiotic use, feeding type, etc.), we will adjust it with RDA.

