### Sample size

The purpose of this study is to detect the alpha diversity of gut microbiota in preterm infants (Shannon index is a better indicator of species richness and evenness) and group differences in short chain fatty acids of interest. At present, no study has reported the effect of OAC on the difference in alpha diversity of gut microbiota and metabolites between preterm infants receiving oropharyngeal administration of colostrum and those receiving sterile water. Therefore, it is difficult to estimate the expected change. However, clinically relevant differences in the Shannon index have been determined based on previous studies on the effect of different feeding types on the Shannon index of preterm infants at the 7th day of age [46–49]. According to these studies, the mean between-group difference in Shannon index ranged from 0.2 to 0.6 with a standard deviation of 0.2 to 0.8 and a mode of 0.6 [46–49]. In a study of the effect of OAC on oral microbiota, the mean between-group difference in Shannon index ranged from 0.2 to 0.5 [50]. Combined with these basic data, the mean difference in Shannon index is assumed to be 0.2, with a standard deviation of 0.6. We conducted sample size estimation using PASS 15.0 (NCSS, Kaysville, Utah, United States). To achieve a statistical power of 80% (2-sided type 1 error of 0.05), the calculated sample size of 143 patients for each group (286 in total) with a ratio of 1:1 will be used. In addition, the relevant difference in short chain fatty acids is based on the previous difference of acetic acid, the main metabolite of preterm infants at the 7th day of life with different feeding types. The mean value of the difference between groups of acetic acid is about 0.025 µmol/g, with a standard deviation of 0.02–0.1 for each group [51, 52]. Therefore, a sample of 92 infants in each group (184 in total) will provide 80% power to detect a difference in short chain fatty acids of at least 0.025, assuming a standard deviation of 0.06 and a 2-sided type I error of 0.05. In combination with these two sample sizes, we will use a relatively larger sample (143 cases). Assuming a loss of 10–12% to follow-up, we will need to include 160 infants in each group, resulting in a total sample size of 320. The sample size will be adjusted based on the results of interim analysis.

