### Data collection

Descriptive and clinical data be collected from both groups. Birth status characteristics, such as delivery mode, gestational age, weight and length, Apgar score will be collected in addition to the mothers’ occupation, education level, disease, use of drugs, supplements and antibiotics. During hospitalization, clinical data will be collected on enteral feeding (start time, duration, starting dose, feeding type and total enteral feeding time); parenteral nutrition (start time and duration); antibiotics use in infants (type, start time, duration and dose); NEC, LOS and mortality; and respiratory support.

We hypothesize that OAC would regulate gut microbiota and its metabolites in very preterm infants, resulting in an increase in microbial diversity, with increasing dominance of Lactobacillus/Bifidobacterium predominating and a relative decrease in Proteus species. Stool samples will be collected from selected subjects at the first defecation, as well as on the 7th, 14th, 21st and 28th days and immediately frozen at − 80 °C. Fecal samples refrigerated with dry ice will be transported to the Microbiology Research Institute of Shenzhen People’s hospital. After extracting DNA from frozen fecal samples, 16S rRNA gene will be amplified by polymerase chain reaction (PCR) (v3-v4 hypervariable region) and sequenced using Illumina miseq platform. All data collection procedures will be performed following the local coronavirus disease 2019 (COVID-19) epidemic prevention and control policy.

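### For non-normal alpha diversity across time points the plan names Kruskal-Wallis, an independent-samples test, although the stools are serial samples from the same infants

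*Protocol article*

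**What the plan says.** The Data collection section sets the sampling scheme: "Stool samples will be collected from selected subjects at the first defecation, as well as on the 7th, 14th, 21st and 28th days". Each infant can therefore contribute up to five stools, and the Study design section gives the same schedule.

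For change over time, one sentence in the Statistical analysis section sets both branches. The normal branch is "Repeated measures analysis of variance (ANOVA) (for normally distributed data". The non-normal branch is "Kruskal Wallis test (for non-normal data) will be used to evaluate the microbial alpha diversity at different time points". The significance rule in the same section is "Values with *p* < 0.05 will be considered statistically significant".

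The comparison of arms is specified separately. Outcome 2b concerns "between-group differences in alpha diversity of gut microbiota measured using Shannon index, Simpson index and Chao1 index on the 14th, 21st and 28th days", and Table 1 assigns it a t-test or Wilcoxon test between groups. Table 1 lists neither Kruskal-Wallis nor repeated-measures ANOVA for any outcome, so the sentence at issue describes a supporting analysis.

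**The concern.** The two branches address the same question on the same data, but only one respects the structure of those data. Repeated-measures ANOVA treats the infant as the repeated unit. Kruskal-Wallis treats the five sets of stools as if they came from five unrelated groups of infants. It generalises the two-sample rank-sum test and is not the rank counterpart of repeated-measures ANOVA. This is a named test that does not fit, rather than a detail left to an analysis plan that is not shown.

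The article names no rank test for several dependent time points elsewhere. A Wilcoxon test within individuals is mentioned, but it is not said to be paired and does not cover five times jointly.

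What is at stake is how an across-time result is read. In the non-normal branch, a non-significant result could reflect the test rather than the infants. The same data would also face very different actual error rates depending on how a normality check falls.

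**Working it through.** **Inputs from the article.** Five stool times (Data collection); significance level 0.05 (Statistical analysis); for the Shannon index, "the mean difference in Shannon index is assumed to be 0.2, with a standard deviation of 0.6"; and "the calculated sample size of 143 patients for each group (286 in total) with a ratio of 1:1" (both Sample size).

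**Input not in the article.** The within-infant correlation ρ of the diversity index. It is assumed exchangeable and shown over 0.3, 0.5 and 0.7.

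**Step 1: the plan's own figure.** n per group = 2 × (1.960 + 0.842)² × (0.6/0.2)² = 2 × 7.85 × 9 = 141.3, so 142 by the normal approximation. The t-test version gives 142.2, so 143, as stated; power at 143 is 0.805. This figure belongs to the day-7 comparison of arms. The article states no error rate or power for the across-time analysis.

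**Step 2: type I error, approximate formula.** With no change over time, the time means within an infant differ only through the within-infant part of the variance, a share of 1 − ρ. Kruskal-Wallis scales by the total variance. Its statistic therefore behaves roughly as (1 − ρ) times a chi-square on 4 degrees of freedom, and the actual error is P(χ²₄ > 9.488/(1 − ρ)). For 4 degrees of freedom, P(χ²₄ > x) = exp(−x/2)(1 + x/2).

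- ρ = 0.3: x = 13.55, giving 0.9%
- ρ = 0.5: x = 18.98, giving 0.08%
- ρ = 0.7: x = 31.63, giving less than 0.001%

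**Step 3: type I error by simulation** (143 infants, five times, normal data, 4,000 runs).

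| ρ | Kruskal-Wallis | Friedman |
|---|---|---|
| 0.3 | 0.8% | 4.7% |
| 0.5 | 0.1% | 4.8% |
| 0.7 | 0.0% | 5.0% |

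Skewed data give 1.2%, 0.1% and 0.0% for Kruskal-Wallis. Four time points, or 286 infants, give the same pattern.

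**Step 4: power by simulation** (five times, linear change, SD 0.6, 2,000 runs; Kruskal-Wallis / Friedman). The article does not say whether the analysis is run within each arm or over both arms, so both are shown.

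| Total change | Infants | ρ = 0.3 | ρ = 0.5 | ρ = 0.7 |
|---|---|---|---|---|
| 0.2 | 143 | 66% / 77% | 62% / 91% | 60% / 99% |
| 0.1 | 143 | 11% / 22% | 5% / 32% | 1% / 51% |
| 0.2 | 286 | 96% / 98% | 98% / 100% | 99% / 100% |
| 0.1 | 286 | 28% / 44% | 21% / 62% | 11% / 85% |

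Repeat runs agree with the one-arm figures to within about 3 percentage points. In one arm, Friedman gains from higher correlation while Kruskal-Wallis loses.

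**The case against.** The strongest reply is that little depends on this sentence. It supports no outcome listed in Table 1, it applies only when data are non-normal, and its error is conservative, so it cannot produce a false claim of benefit. All of that stands, and it limits the weight of the point. It does not make an independent-samples test suitable for serial samples.

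A reader might also infer several stronger things that the article does not support:

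- **That outcome 2b is compromised.** It is not. It compares the arms on each named day by t-test or Wilcoxon test. On any one day the arms are independent samples, so that test is valid and does not rely on Kruskal-Wallis.
- **That false positives are inflated.** If all five stools per infant were pooled to compare arms as though independent, simulated type I error would be about 18–32% for ρ of 0.3 to 0.7. The article describes no such pooling.
- **That the ANOVA branch would discard much of the sample.** If 10% of stools were missing independently at each of five times, 0.9⁵ = 0.59 of infants would have complete series. That missing rate is not in the article. The Sample size section gives only a 10–12% loss overall, and the Missing data section plans doubly robust inverse probability weighting rather than plain deletion.
- **That the analysis has little power in general.** This is true only for small changes or, in relative terms, high correlation. For a 0.2-unit change the test keeps 60–66% in one arm and 96–99% over both.

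**Conclusion.** The point holds as a narrow error in a stated rule. Kruskal-Wallis is the wrong test for repeated stools from the same infants. At ρ of 0.3 to 0.7 its actual error is about 1% or less against a nominal 5%. In one arm it gives up roughly 11 to 39 percentage points of power for a 0.2-unit change (77 − 66 and 99 − 60). For a 0.1-unit change it gives up 11 to 50 points (22 − 11 and 51 − 1).

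These sizes rest on an assumed exchangeable correlation, a linear change and complete series. At ρ = 0 Kruskal-Wallis is valid (4.5%) and there is no loss; at ρ = 0.2 its error is 2.1% and the power loss for a 0.2-unit change in one arm is small (68% against 72%). The 0.2 figure is the article's planning difference between arms, borrowed here as a scale for change over time.

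The day-7 primary outcomes, the comparisons in 2b and the sample size are untouched. The correction is worth making because the rule is wrong as written and cheap to put right.

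**What to change.** In the Statistical analysis sentence, replace Kruskal-Wallis with a method for dependent data. For infants with all stools, the Friedman test is enough. Where stools are missing, use a rank-based longitudinal model, or a linear mixed model on a suitably transformed index if it is skewed. Either model should take the infant as the repeated unit, include arm, day and arm-by-day terms, and use every available stool. The mixed model could also replace both branches, so that the method no longer turns on a normality check, but that is optional. Correcting the error requires only the replacement of Kruskal-Wallis.

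The cost is one sentence of analysis wording. Standard software covers all of these methods, and no new data, visits or infants are needed.

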The microbiome-metabolome association is bidirectional [30]. Host and gut microbiota interact through either symbiosis or imbalance of small molecule metabolites. Metabonomics is undoubtedly a promising method to study the interaction between host and gut microbiota [31]. Metabolites of bacteria may also be novel therapeutic targets for human chronic diseases [32]. Several previous studies have investigated the effect of OAC on enteral feeding, NEC, LOS, mortality, etc. [33–39]. Because of limited sample size and inconsistent OAC measures, among other reasons, there is no sufficient evidence to prove that OAC can reduce the incidence of NEC, LOS and death [40]. But OAC can promote intestinal maturation and rapidly achieve total enteral feeding [41, 42]. However, the mechanism by which OAC promotes intestinal maturation by changing intestinal microbiota and metabolites remains elusive, which is the significant contribution of our study.

We hypothesized that OAC could promote relative enrichment of intestinal Firmicutes but reduce relative enrichment of Proteobacteria. In addition, the production of short chain fatty acids and other metabolites would change accordingly to resemble the gut microbiota profile in normal full-term breast fed infants, improving the health outcomes of preterm infants. The purpose of this multicenter, double-blind, randomized controlled trial is to evaluate whether OAC can modulate gut microbiota diversity and metabolites (such as short chain fatty acids) compared with oral care with sterile water.

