2c Between-group differences in the concentration of fecal metabolites at the 14th, 21st and 28th days of life		Short chain fatty acids (continuous)	Individuals: FC, PCA/PLS-DA Intergroup: T/Wilcoxon text
2d Proportion of gut microbiota (phylum and genus level)		The percentile of gut microbiota at the phylum and genus levels of the total microbiota (binary)	Individuals: Wilcoxon text; Intergroup: Chi-square test
2e Gut microbial beta diversity		Bray–Curtis distances with 9999 permutations (continuous)	PCOA; LDA
2f Correlation between dominant microbiota and metabolites		Correlation between dominant microbiota and metabolites	Partial Least Squares Discriminant Analysis

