Gut microbiota can regulate the signal pathways regulating intestinal mucosal homeostasis through the production of metabolites. Non-targeted LC–MS will be used to evaluate short chain fatty acids and other organic acids and alcohols. The relative and absolute concentrations of metabolites will be calculated using fold change (FC) value, and the difference in metabolite expression between the two groups will be explored. Principal component analysis or partial least squares discriminant analysis will be used to compare different metabolites among the sample types. A time dynamic curve will be used to further analyze metabolites of interest. The correlation between the relative abundance of dominant bacterial taxa based on 16S rRNA gene sequencing and the intensity of metabolites of interest will be determined using sparse partial least squares regression [45].

Details of all methods of analysis are provided in Table 1.

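### Outcome 2d types phylum and genus shares as binary and gives them a chi-square or Fisher test with no stated counting unit, though each infant contributes a continuous value

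*Protocol article*

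**What the plan says.** The Statistical analysis section of the protocol article states: "The proportion difference of gut microbiota at the phylum and genus levels will be calculated using chi-square" or Fisher's exact test. The next sentence sets the threshold: "Values with *p* < 0.05 will be considered statistically significant".

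Table 1, row 2d, gives the outcome measure as "The percentile of gut microbiota at the phylum and genus levels of the total microbiota (binary" (closing bracket omitted here) and the methods as "Individuals: Wilcoxon text; Intergroup: Chi-square test".

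The same section also plans a separate screen for taxa: "We will use Linear discriminant analysis (LDA) of effect size (LEfSe) to determine the most discriminant taxa between the two groups". For the link with metabolites, the plan takes "The correlation between the relative abundance of dominant bacterial taxa based on 16S rRNA gene sequencing" into a sparse partial least squares regression. The Background gives the hypothesis that outcome 2d bears on: "OAC could promote relative enrichment of intestinal Firmicutes but reduce relative enrichment of Proteobacteria".

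**The concern.** A taxon's share of an infant's microbiota is a number between 0 and 1, obtained once per stool. It is not a yes/no outcome, and a chi-square or Fisher test needs counts of independent units. The text and Table 1 agree on the test, so this is not a slip in one cell.

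The choice also departs from the article's own practice in three places:

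- For baseline data, chi-square and Fisher are kept for categorical factors, and continuous variables get a t-test or Wilcoxon test.
- Row 2d uses Wilcoxon within individuals but chi-square between groups for the same variable.
- The metabolite analysis treats relative abundance as a quantitative variable.

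Because the counting unit is not stated, the same sentence could be carried out in ways that behave very differently. At stake is whether a reported difference in Firmicutes, Proteobacteria or any genus can be believed, and whether a real one could be found.

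**Working it through.** **Inputs from the article.** 143 infants per arm (Sample size section) and a nominal two-sided 0.05. The article gives no operating figure for the taxon comparisons. Its own sample size does reproduce: for a Shannon difference of 0.2 and SD 0.6 at 80% power, the normal approximation gives 2 × 0.6² × (1.96 + 0.84)² / 0.2² ≈ 141.1, or 142 with unrounded normal quantiles and rounding up. The t-based solution is 142.25, hence 143 as stated.

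**Assumptions, because the article gives neither depth nor between-infant variation.** Reads per sample M = 1,000 to 30,000; intra-infant correlation of reads ρ = 0.001 to 0.5; mean taxon share μ = 2%, 10% or 30%, equal in both arms. Shares follow a beta distribution across infants with SD = √(ρμ(1−μ)). At μ = 30%, ρ = 0.05 means an SD of 0.102 and ρ = 0.5 an SD of 0.324.

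**Reading (a): reads pooled over infants.** Pooling inflates the variance by 1 + (M−1)ρ, so the null rejection rate is 2 × [1 − Φ(1.96 / √(1 + (M−1)ρ))].

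- Example: M = 1,000 and ρ = 0.05 give 1 + 999 × 0.05 = 50.95; the square root is 7.14; 1.96 / 7.14 = 0.275; the rate is 78.4%.
- Formula values, with the range over the three mean shares from a simulation of 2,000 runs per cell in brackets:

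| ρ | 1,000 reads | 10,000 reads | 30,000 reads |
|---|---|---|---|
| 0.001 | 16.6% (15.4-16.8) | 55.5% (55.4-57.4) | 72.5% (72.2-73.8) |
| 0.01 | 55.4% (56.2-57.0) | 84.5% (84.1-85.6) | 91.0% (89.4-91.6) |
| 0.05 | 78.4% (79.0-79.3) | 93.0% (92.5-93.5) | 96.0% (95.4-97.0) |
| 0.1 | 84.5% (84.5-84.8) | 95.1% (94.6-95.6) | 97.1% (96.4-97.7) |
| 0.3 | 91.0% (90.7-91.0) | 97.1% (96.5-97.2) | 98.4% (98.4-98.5) |
| 0.5 | 93.0% (92.7-93.4) | 97.8% (97.4-97.8) | 98.7% (98.7-99.1) |

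The mean share hardly matters; ρ and depth do.

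**Reading (b): each infant classed yes or no.** In the same simulation at 30,000 reads, null rejection is 0-5.3% for presence or absence and 3.6-5.6% for above or below the mean share. The error is not inflated. The cost is lost information: for normally distributed data a median split keeps 2/π ≈ 64% efficiency, so 143 per arm would act like about 143 × 0.64 ≈ 91. Shares are bounded and usually skewed, and no median split is planned, so this is only a benchmark.

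**Reading (c): mean percentages entered as counts.** Null rejection is 0-0.2% with counts out of 100 and 0-0.6% with counts out of 143. The test is far too conservative.

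**Infant as unit, continuous share.** Null rejection is 3.2-6.6% for Wilcoxon (500 runs per cell, Monte Carlo standard error about 1 point) and 4.4-5.8% for the t-test. Both are consistent with 5%.

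**The case against.** A reader might infer that the plan counts sequence reads as if they were patients, and so will declare almost every null taxon significant. The article does not support that as a statement of fact. It nowhere says that reads are pooled. The wording about the total microbiota hints at reads as the denominator, but other cues point the other way. The label binary is how a per-infant yes/no outcome would be typed. The chi-square/Fisher pair is the one used for infant-level factors such as sex and delivery mode. Fisher's test is meant for small counts, whereas 143 infants at 10,000 reads would be 1.43 million reads per arm. The inflation therefore applies under one reading of three, and its size rests on assumed depth and correlation.

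It is also fair to say that 2d is a secondary outcome, that the primary outcomes are the day-7 Shannon index and short chain fatty acids, and that LEfSe and Adonis also examine composition. These points limit the consequence. They do not rescue 2d, because neither method replaces the chi-square test assigned to it.

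A reader might also fault the lack of a multiplicity rule across taxa. That may sit in an analysis plan that is not shown, so it is no part of this finding. Nor does the article require Firmicutes and Proteobacteria to be the confirmatory taxa: the Data collection section hypothesises about Lactobacillus/Bifidobacterium and Proteus.

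**Conclusion.** The point holds in this form: outcome 2d is wrongly typed as binary, is assigned a test unsuited to a continuous per-infant share, and has no defined unit of analysis. Depending on how the sentence is carried out, null rejection at a nominal 5% could lie anywhere from near 0% to about 99%. The upper end applies only if reads are pooled and the assumed correlation and depth are realistic. Under the per-infant yes/no reading, the fault is lost information and an unstated cut-off that could be chosen after seeing the data, not false positives.

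This should be fixed, but it does not threaten the trial's main conclusions. It concerns one secondary outcome, though one that bears on the Firmicutes/Proteobacteria hypothesis. The primary outcomes and the sample size are unaffected.

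**What to change.** In Table 1, row 2d, change binary to continuous and describe the measure as each infant's relative abundance of the taxon in a given stool. In that row and in the Statistical analysis section, replace the chi-square/Fisher comparison with a between-arm comparison of per-infant relative abundance at each time point, using the Wilcoxon test that the plan already lists for its other continuous outcomes.

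A false discovery rate adjustment within the phylum and genus levels would be a sensible addition if the analysis plan does not already have one.

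The cost is a wording change and standard software, with no new data. It should be made before any analysis by arm.

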## Discussion

This multicenter, double-blind RCT study will be performed based on 16sRNA gene sequencing and non-targeted metabolic mass spectrometry. The purpose of the trial is to evaluate the effect of OAC on the gut microbiota and metabolites of preterm infants.

OAC often occurs before or in the early stage of enteral feeding of preterm infants. Previous studies have confirmed that OAC is safe and effective [54]. It increases IgA, IgM, and lactoferrin, to regulate the immune function [55]. The role of human microbiota and metabolic activities in health and disease have been revealed through the application of new technologies. However, the effect of OAC on gut microbiota and metabolites is not clear. Previous studies have suggested that microbiota regulate the development of the immune system and brain in newborns [56]. Therefore, we hypothesized that OAC can increase intestinal bacterial diversity, promote the abundance of Bifidobacteria and other dominant microbiota, as well as the production of short chain fatty acids, thereby reduce vascular damage caused by oxidative stress [57]. It can also protect the intestinal barrier integrity and prevent the occurrence of preterm infant-related diseases by modulating the brain-gut axis.

It should be noted that the gut microbiota are affected by many factors. Previous studies have shown that infants receiving antibiotic treatment have increased relative abundance of Proteobacteria, and decreased the relative abundance of Actinobacteria, Firmicutes, and Bacteroidetes decreases [23]. The relative abundance of Bacteroides decreased after cesarean section and was higher during vaginal delivery [58]. Formula-fed infants showed higher relative abundance of Firmicutes, whereas breast-fed infants showed increased abundance of the phyla Actinobacteria and the genus Bifidobacterium [59]. Therefore, we plan to conduct a multicenter, double-blind RCT study to evaluate the effect of OAC on the gut microbiota and metabolites of preterm infants. The design of the proposed study considers group differences in mode of delivery, antibiotic exposure, feeding type, among other factors to evaluate the effectiveness of OAC comprehensively. The relationship between bacterial species composition and environmental variables is determined by controlling some environmental factors which affect gut microbiota imbalance using statistical methods such as RDA.

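### Redundancy analysis has two roles that do not fit together: finding factors within each arm, and adjusting the OAC effect, which needs both arms in one model

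*Protocol article*

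**What the plan says.** All the relevant text is in the protocol article.

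- **Statistical analysis, first use of RDA.** It will be run in the Vegan package "to define the factors that could significantly affect gut microbial composition in each group".
- **Statistical analysis, second use, two sentences later.** If the OAC effect turns out smaller than that of other factors ("delivery mode, antibiotic use, feeding type, etc"), "we will adjust it with RDA".
- **Discussion.** The same technique is described as a means of "controlling some environmental factors which affect gut microbiota imbalance using statistical methods such as RDA".
- **Statistical analysis, between-arm test.** Adonis permutational analysis of variance on Bray-Curtis distances, with 9999 permutations, "will be used to compare microbial community structure between each of the two groups". LEfSe is assigned to finding the taxa that separate the arms.
- **Statistical analysis, threshold.** Values below 0.05 "will be considered statistically significant".
- **Table 1.** RDA does not appear. The beta-diversity row lists principal co-ordinates analysis and linear discriminant analysis.

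**The concern.** The two uses of RDA need different models. A model fitted inside one arm cannot contain treatment, because treatment does not vary there. Such a model can neither rank OAC against delivery mode nor adjust the OAC effect for it. The only RDA whose scope the text describes is the per-group one. The adjustment RDA is mentioned, but nothing says which infants or terms it contains.

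Three things are at stake. Each per-arm fit uses half the sample, which wastes information on factors that act alike in both arms. Two separate sets of significance verdicts contain no test of whether a factor's influence depends on OAC, which is the comparative question a two-arm trial invites. And the adjustment, as worded, cannot be obtained from the per-group fits.

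**Working it through.** **1. The two roles side by side.**

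| Use of RDA | Infants needed | Can OAC be a term? |
|---|---|---|
| Factors that matter in each group | one arm at a time | no, it is constant |
| Weigh OAC against other factors, then adjust | both arms together | yes, it must be |

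One set of fits cannot serve both rows.

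**2. Infants available per arm.** The protocol gives no figure for the RDA, so the Shannon calculation supplies the sample size. Its inputs are in Sample size: "the mean difference in Shannon index is assumed to be 0.2, with a standard deviation of 0.6", two-sided alpha 0.05, power 80%.

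n per group = 2 × (1.960 + 0.842)² × 0.6² / 0.2² = 2 × 7.85 × 9 = 141.3, so 142 by the normal approximation. The t-test version gives 142.2, rounded up to 143. The protocol's 143 per group (286 in total) is reproduced.

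**3. What halving the sample does to one factor.** Assume a factor with the same true effect in both arms. The pooled power is an assumption, as the protocol states none.

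- Non-centrality in 286 infants = 1.960 + z(power).
- Non-centrality in one arm of 143 = pooled value / √2.
- Power in one arm, p = Φ(per-arm non-centrality − 1.960).
- Probability of significance in exactly one arm = 2p(1 − p).

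| Assumed pooled power | Pooled non-centrality | Per-arm non-centrality | Per-arm power | Significant in exactly one arm |
|---|---|---|---|---|
| 80% | 2.80 | 1.98 | 50.8% | 50% |
| 90% | 3.24 | 2.29 | 63% | 46.6% |
| no effect | 0 | 0 | 5% | 9.5% |

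With no true effect of any of the three named factors, and the factors taken as independent, at least one differs between the two lists with probability 1 − (1 − 0.095)³ = 25.9%.

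**4. Check with a permutation test.** The formula above is for a one-parameter z-test, so a one-factor RDA permutation test was simulated at 143 per arm, with identical effects in both arms (300 replicates, 199 permutations, 10 response variables, a balanced binary factor). Disagreement was 7% at per-arm detection of 4%, 35% at 25%, 50% at 49%, and 27% at 83%. This agrees with 2p(1 − p).

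**5. What a direct interaction test can do.** If the pooled standard error of a factor effect is s, each arm's is s√2 and the difference between arms has standard error 2s. An interaction as large as the effect that has 80% pooled power therefore has non-centrality 2.80 / 2 = 1.40 and power Φ(1.40 − 1.96), about 29%. The test is valid but weak.

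**The case against.** The strongest reply is that the harm is not written into the plan. A reader might infer that the trial will show two differing factor lists and present the difference as something OAC did. No section says the lists will be compared. Between-arm questions are given to Adonis and LEfSe, and Adonis is a valid comparison of the arms. Describing influential factors within a group is a legitimate aim in itself. All of this stands, so the 50% is the size of a foreseeable misreading and not an error rate of a planned analysis.

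A reader might also infer that OAC is absent from every RDA. The text does not support that: the adjustment use weighs OAC against other factors and so implies both arms. What remains is that this second model is not reconciled with the first.

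The authors also use the word *each* loosely: the Adonis sentence speaks of a comparison "will be used to compare microbial community structure between each of the two groups", although it plainly concerns both arms at once. Within-arm fitting is thus the natural reading of the RDA sentence but not the only possible one. That is a reason to settle the wording.

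Finally, one could argue that RDA is Euclidean while Adonis uses Bray-Curtis, so the effects lie on different scales. The article names neither a distance nor a transformation for RDA, and a condensed article may leave that to the full plan. It is not counted as a fault here.

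**Conclusion.** The point holds as an inconsistency in an exploratory analysis. RDA is asked to work within each arm and also to adjust a between-arm effect, and no single stated model does both. Per-arm fits give up half the sample each and provide no valid test of a differing factor effect.

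The size, if someone did compare the lists, is about 50% one-arm-only significance for an identical effect with 80% pooled power, 46.6% with 90%, and 9.5% per factor with no effect. These figures rest on assumed powers, and the 25.9% for three factors also rests on independence. The protocol supplies only the 143 per arm.

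The consequence is confined to the exploratory analysis of community composition. The primary outcomes (Shannon index and short chain fatty acids at day 7) and the Adonis test are untouched. The change is worth making because it costs almost nothing.

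**What to change.** - Delete the restriction to each group. At each stool day, fit one RDA to both arms, preferably the distance-based form on the same Bray-Curtis matrix as Adonis, so that all effects share one scale.
- Include arm, gestational-age stratum and factors fixed before randomisation, such as delivery mode.
- State that a factor acts differently by arm only on the permutation test of the arm-by-factor term, and label that test exploratory.
- Infant antibiotic use and feeding type after randomisation may themselves be affected by OAC. Report them descriptively or in a separate sensitivity model, not as adjustment of the OAC effect.
- Amend the Discussion sentence on RDA to match.

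The rule that makes adjustment depend on the relative size of the OAC effect is a separate matter, although the same pooled model would serve there too.

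The cost is plan wording and a different model formula in the same package, with no new data. The downside is a few extra exploratory interaction tests with low power (about 29% in the illustration above), so a non-significant interaction must not be read as evidence that a factor acts equally in both arms.
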